#### Primary outcome measures cluster RCT

The first primary outcome measure is *social participation *measured with the Birchwood Social Functioning Scale (SFS) [44]. It measures social functioning on seven domains: social engagement/withdrawal, interpersonal behavior, pro-social activities, recreation, independence-competence, independence-performance, and employment/occupation. The SFS is a reliable, valid, sensitive to change, instrument with a high internal consistency (α = 0.80) [44].

The second primary outcome measure is victimization related to societal participation and includes the following:2.*Criminal victimization* will be measured with the Dutch version of the Safety Monitor, developed by the Dutch Ministry of Security and Justice [45], and strongly resembles the International Crime Victimization Survey [46]. It is a self-report questionnaire in which section 4 measures victimization on 15 crimes: burglary, theft from car, car theft, theft of other motorized vehicles, bicycle theft, (attempt to) robbery, theft (other than previously categorized), sexual intimidation or assault, threats (of violence), physical assault, vandalism, identity fraud, fraud with buying/selling items/services, hacking, cyber bullying. For each incident reported in the past 12 months, participants are asked to give more information about the incident.3.*Perceived safety* will also be measured with the Safety Monitor. The participant is asked whether they ever feel unsafe (yes/no) and how often (often/sometimes/rarely).4.*Discrimination and stigmatization* is assessed by the Discrimination and Stigmatization Scale (DISC-12) [47]. This scale consists of four subscales: unfair treatment, stopping self, overcoming stigma, positive treatment. The DISC-12 contains 32 items answered on a 4-point scale ranging from ‘no difference (0)’ to ‘a lot (3)’. A ‘not applicable’ answer is available when the participant was not involved in the described situation. Psychometric properties are considered good, Cronbach’s alpha is 0.78 and the inter-rater reliability ranges from 0.62 to 0.95.

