### RCT analyses

#### Sample size

Sample size is calculated using the model of Twisk [56]. This model is suitable for multiple measurements over time, but can also be used for cluster randomization. With the ratio of the number of subjects in the compared groups being 1 (*r*), a correlation coefficient of the repeated measurements of 0.20 (ρ), a conservative difference between the groups in the mean value of social functioning of 0.25 (*v*), and a power of 1-β = 0.80, the number of participants needed is 151 for each condition at T2 measurement (α = 0.05, two-tailed). Taking into account an attrition rate of 15% for loss due to follow-up or consent withdrawal, 173 participants per condition need to be recruited to achieve the required power.$$ N=\frac{Z\left(1-\alpha /2\right)+Z\left(1-\beta \right)\ 2\ \sigma 2\left(r+1\right)\left[1+\left(T-1\right)\rho \right]}{v2r\ T} $$

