#### Statistical analyses

Data will be analyzed according to the ‘intention to treat’ principle, meaning that F-ACT teams (and thus clients) that are assigned to either experimental or control condition in randomization, will be analyzed accordingly. Because of the cluster design and multiple measurements over time, generalized linear mixed models (GLMM) will be used with SPSS (version 22); depending on the distribution of the outcome variable a logistic regression model or a linear regression model will be adopted. GLMM is robust with respect to missing data [57], which is not uncommon in research among outpatients with SMI. Therefore, multiple imputation is not necessary. To analyze the effect of the Victoria intervention on the main outcomes, differences in societal participation and victimization, both conditions will be compared after 9 and 18 months follow-up with time as a categorical variable. Measurements over time are nested within participants; therefore, random slopes will be added for time. Random intercepts will be added for the participants. The same procedure will be adopted for secondary outcome measures. Furthermore, possible confounders will be examined, such as socio-demographic characteristics, current diagnosis, number of years in MHC, or perpetration on whether they need to be added to the model. Only significant confounders will be added to the final model. In all analyses performed, two-tailed *p*-values < 0.05 are considered significant. Finally, Akaike’s Information Criterion (AIC) will be used for the selection of the final model that fits the data best and is the most generalizable [58].

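### Two primary domains, measured by four instruments at two follow-ups, are all tested at an unadjusted 0.05 with no order or success rule, so the chance of a false-positive primary result is well above 5% (up to about 34%)

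*Protocol article*

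**What the plan says.** All references are to the protocol article.

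- **Primary outcomes.** Table 1 lists four instruments under primary outcome measures: the SFS, Safety Monitor section 4 (criminal victimization), the DISC-12, and Safety Monitor section 3 (perceived safety). The section on primary outcome measures groups the same four into two domains. Social participation, by SFS, is the first. For the rest it says: "The second primary outcome measure is victimization related to societal participation and includes the following", followed by the three remaining measures. No composite and no lead measure is named among those three.
- **Comparison.** Under Statistical analyses, the arms are compared at both follow-ups, 9 and 18 months, in a mixed model with categorical time. Neither time point is called primary.
- **Threshold.** The same section states: "In all analyses performed, two-tailed *p*-values < 0.05 are considered significant".
- **Sample size.** It rests on one outcome, "a conservative difference between the groups in the mean value of social functioning of 0.25", with "a power of 1-β = 0.80" and the full, unsplit "α = 0.05, two-tailed".
- **Research question.** The primary effectiveness question joins more participation and less victimization with the word and. No passage says whether both must be shown or whether one is enough.

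**The concern.** A 5% threshold per test gives a 5% error rate for the trial's answer only if one test carries that answer, or if a rule links the tests. Here several measures and two follow-ups all count as primary, each has its own 5%, and nothing ranks them. A single p-value below 0.05, for example on perceived safety at 9 months, could be presented as a primary result while SFS, the only outcome with a power calculation, shows nothing.

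This is not a detail left to an analysis plan that is not shown. The article itself sets the unadjusted threshold for all analyses, so a later hierarchy or Holm procedure would contradict its text. The conclusion is meant to carry weight: the Discussion says that the results may validate the intervention and counts sufficient power among the study's strengths.

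**Working it through.** **1. The plan's own figure.** Inputs from the Sample size section: α = 0.05 two-sided, power 0.80, difference v = 0.25, ratio r = 1, correlation of repeated measurements ρ = 0.20. The article gives neither σ nor T. I take σ = 1, that is, v as a standardised difference, and try values of T.

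N per arm = (z₁₋α/₂ + z₁₋β)² σ² (r+1) [1+(T−1)ρ] / (v² r T), with (1.960 + 0.842)² = 7.849

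- T = 1: 7.849 × 2 × 1.0 / (0.0625 × 1) = 251.2
- T = 2: 7.849 × 2 × 1.2 / (0.0625 × 2) = 150.7, rounded up to **151**, the stated figure
- T = 3: 7.849 × 2 × 1.4 / (0.0625 × 3) = 117.2

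Only T = 2 reproduces the plan. The 151 per arm therefore corresponds to an SFS effect over two measurements, most naturally the two follow-ups. For one time point on the same formula, power at 151 per arm is Φ(0.25 × √(151/2) − 1.960) = Φ(0.212), about 58%.

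**2. Chance of at least one false positive, independent tests.** 1 − 0.95^k:

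- k = 4 (four measures, one test each): 1 − 0.8145 = 18.5%
- k = 8 (four measures, two follow-ups): 1 − 0.6634 = 33.7%

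**3. Allowing for correlation.** The article gives no correlations between outcomes, so these are assumptions: 0 to 0.7 between outcomes and 0.2 to 0.7 between the two time points. Simulating correlated normal test statistics with no true effect (500,000 draws per setting) gave:

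| | Either direction | Favouring the intervention only |
|---|---|---|
| 8 tests | 20.8% to 33.4% | 10.5% to 18.0% |
| 4 tests, one time point | 13.0% to 18.6% | 6.5% to 9.7% |
| Nominal | 5% | 2.5% |

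**4. What adjustment does to SFS power at 151 per arm.** With T = 2 the standardised signal is 0.25 × √(151 / (2 × 0.6)) = 2.804.

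- α = 0.05: Φ(2.804 − 1.960) = 80%
- α = 0.0125 (Bonferroni over four, or the first Holm step): Φ(2.804 − 2.498) = 62%
- Restoring 80% power at α = 0.0125 needs 215 per arm, or 215 / 0.85 = 253 with 15% attrition

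A fixed sequence that starts with SFS at 0.05 keeps the first line.

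**The case against.** The best defence has four parts.

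*The article states a per-test threshold, not a success rule.* This stands. A reader might infer that any single significant result is enough for a claim of effectiveness, but the text does not say so, and the word and in the research question could mean that both domains are required. Under that reading, with independent tests at both follow-ups and no true effect anywhere, the chance of passing both domains is about (1 − 0.95²) × (1 − 0.95⁶) = 0.0975 × 0.265 = 2.6%. But the requirement is not stated. It also leaves the victimization domain open: three measures at two follow-ups give a 26.5% chance of a false positive there, even if participation truly improves.

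*Eight tests is one reading.* This also stands. The section on primary outcome measures speaks of two primary outcomes, and four is the count in Table 1. A joint test over time for each measure is not excluded; that would give four tests and 18.5%. Eight is the count when each time point is tested separately, not a minimum.

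*The DISC-12 score is not fixed.* A reader might count the unnamed subscale as a further fault. A condensed article can leave that choice to a fuller document, so it is not part of this point.

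*This is an initial trial with a process evaluation beside it.* That lowers the stakes somewhat, but the article still asks a primary effectiveness question and sets a significance threshold for it.

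None of this removes the core: several primary measures, an unadjusted threshold stated for all of them, and no rule linking them.

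**Conclusion.** The point holds in this form: the stated rule puts the chance of at least one false-positive primary result well above 5%. It is 18.5% for four and 33.7% for eight independent tests. Under the assumed correlations it is about 21% to 33% for eight tests, and about 10% to 18% when only results in the intervention's favour count. The eight-test figures assume that each measure is tested at each follow-up. The power figures assume σ = 1 and T = 2 and use the plan's formula as it stands, without a separate term for clustering by team.

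A reader might go further and infer that a chance primary success is likely. The figures do not support that: the risk stays below 50% in every case computed, and a false success in the favourable direction is at most about 18%. The change should be made, since it concerns the primary claim and needs no extra participants.

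**What to change.** In Statistical analyses, replace the blanket 0.05 rule, for the primary outcomes, with a fixed sequence:

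1. SFS at two-sided 0.05, as the group effect over T1 and T2 (the average of the 9- and 18-month contrasts from the planned model).
2. The three victimization measures in an order stated in advance, each at 0.05 and each only if the previous test is significant.
3. Separate time points reported with estimates and intervals as supportive results, without a confirmatory claim.

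The investigators should choose the order of the victimization measures and the DISC-12 score before seeing outcome data by arm.

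**Cost.** A few sentences, with no change to data collection, the SFS alpha or the 151 per arm. Two things are given up. Victimization cannot be claimed as confirmed if SFS fails, and the separate 9- and 18-month comparisons lose confirmatory standing.

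**Alternative.** Holm over the four measures, one test each, also controls the error rate and lets victimization succeed without SFS. In the worst case, when the other measures show nothing, SFS power at 151 per arm could fall from 80% to about 62%.

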## Discussion

Outpatients with SMI experience high rates of victimization, discrimination and stigmatization [11–17]. These adversities are important barriers to rehabilitation and societal participation [21]. This study is the first to evaluate an intervention aiming at recognition of victimization and other adversities, that also targets outpatients’ insight and coping skills with regard to possible risks to ensure safe societal participation. The aim of this first trial on the Victoria intervention is to gain insight into the implementation process and effectiveness of the Victoria intervention in reducing victimization (among other adversities) and increasing societal participation, on both the team level and the client level.

A major strength of this study will be the large sample size of outpatients with SMI, leading to sufficient power, which is often a problem in similar trials [59]. Only clients that are unable to fill out the questionnaire during the inclusion period of 6 months, due to insufficient understanding of the Dutch language, prolonged clinical admission, or severe symptomatology, will be excluded from the study. This, as well as the participation of multiple mental health centers, enhances generalizability of results.

This is, to our knowledge, the first study to address victimization and other adversities as a barrier for societal participation. In relation to this, we incorporated a broad range of outcome measures. Many previous studies on victimization only take into account clinical outcome measures or socio-demographic variables such as living situation [13, 14]. Although some studies include the influence of victimization on, for example, quality of life, this study includes a broad range of social outcome measures, such as social functioning and social support. These outcome measures are likely to be influenced by victimization or other adversities in the social domain [60, 61].

A final strength of the study is the multi-method approach. A process evaluation will be conducted to examine the implementation process of the intervention. Studies with a similar target population that examine complex interventions in a RCT often find no treatment effect, due to, for example, implementation or fidelity issues [62]. Within the design of an RCT, normally, there is little room for examining the implementation process, leading to a black box in explaining the results. Therefore, the UK Medical Research Council advises conducting a process evaluation, to understand context mechanisms and provide insights on implementation and fidelity [63]. For this reason, we do include a process evaluation and a longitudinal follow-up on effects, using a cluster RCT.

One of the main challenges in this study lies in the fact that the Victoria intervention is a complex intervention, encompassing characteristics of the local context, and the complexity of causal relations between intervention and outcomes [36]. MHPs in the participating teams sometimes work in multiple teams or, due to reorganization, they shift from one team to the other. This brings challenges in the implementation of the intervention. To address this, a strong collaboration is created between the two MHC institutions and the university in this project, with shared goals and input. Additionally, the process evaluation will be helpful in following the implementation process.

Another challenge of this study, and of most other studies among outpatients with SMI and follow-up measurements, is the dropout risk in the cluster RCT. In the sample size calculation, we take this into account by estimating a 15% loss to follow-up, and using effect sizes that may be considered conservative, compared to effect sizes found in other studies [64]. This leads to 347 required respondents at baseline measurement. Moreover, with the help of the MHPs, a contact plan, and by giving clients incentives for participating, we aim to prevent dropout as much as possible.

Finally, due to novelty of the Victoria intervention, there is no valid fidelity measure. Therefore, in this project a new fidelity checklist will be developed and used. To increase validity in measuring fidelity, we use triangulation by also including qualitative analyses of the recordings of the supervision meetings and questionnaires for both clients and MHP, as explained in the methods section.

In conclusion, the Victoria intervention is the first to incorporate a positive risk approach into a psychiatric rehabilitation method. This study is expected to provide scientific insights in ways to reduce victimization, (self-) stigmatization and discrimination, and increase societal participation, but also in the impact of other factors such as acknowledgement and awareness of these adversities. Moreover, results of this study may validate the Victoria intervention as one of the practices to better manage risk on adversities related to societal participation.

## Abbreviations

ACT: Assertive Community Treatment
AIC: Akaike’s Information Criterion
BPR: Boston University approach to Psychiatric Rehabilitation
CAU: Care As Usual
DISC-12: Discrimination and Stigmatization Scale
F-ACT: Flexible assertive community treatment
GLMM: Generalized Linear Mixed Models
HoNOS: Health of the Nation Outcome Scale
ISR: Inventory of Social Reliance
LQLP: Lancashire Quality of Life Profile
MANSA: Manchester Short Assessment of Quality of Life
MHC: Mental Health Care
MHCS: Mental Health Confidence Scale
MHP: Mental Health Professional
RCT: Randomized Controlled Trial
SFS: Birchwood Social Functioning Scale
SMI: Severe Mental Illness
TSQ: Trauma Screening Questionnaire
